### Outcome measures

The primary study outcomes are as follows:

Mean size-adjusted bone density Z-scores; TBLH BMC^LBM^ and LS BMAD.^36^
The prevalence of low TBLH BMC^LBM^ and LS BMAD Z-score<−2 at baseline.^36^

Secondary study outcomes are as follows:

Prevalence of low muscle function; grip strength and standing long jump-for-age (Z-score<−2) and musculoskeletal abnormalities/disabilities by HIV status at baseline.Mean percentage change in TBLH BMC^LBM^ (g) and LS BMAD (g/cm^3^), tibial cortical and trabecular volumetric BMD (g/cm^3^), total cross sectional area, cortical thickness and bone strength, muscle mass and function at baseline and 1 year, by HIV status.Assessment of the extent to which pubertal delay explains changes in these bone and muscle outcomes.

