## Introduction

Sub-Saharan Africa (SSA) disproportionally bears the burden of global HIV infection, with nearly 90% of the estimated 2.1 million children under 15 years of age living in SSA.^1^ The global scale-up of antiretroviral therapy (ART) has dramatically improved survival of children with HIV (CWH).^2^ However, there is accumulating evidence that the growing number of these children are now reaching adolescence in SSA with multisystem chronic comorbidities associated with HIV infection and/or its treatment.^3^

Poor linear growth (ie, stunting) is one of the most common manifestations of perinatally (vertically) acquired HIV infection, affecting up to 50% of children.^4 5^ Linear growth is greatest in adolescence during the pubertal development period. Bone mass is thought to change throughout the life course and may be altered by HIV^6 7^ (figure 1). The majority of peak bone mass (PBM), the maximum amount of bone accrued by the end of skeletal maturation, is attained during adolescent growth; by age 18 years in women and age 20 years in men, 80% of PBM is attained.^8^ After PBM is reached, there is no net gain in bone mass. Therefore, PBM is the net reservoir of bone for later life, a key determinant of adult bone mineral density (BMD) and consequently of adult osteoporotic fracture risk.^9^ Linear growth is therefore intimately linked to skeletal development but how HIV infection affects bone development in peripubertal SSA children is largely unknown. The prevalence of low BMD has been found to be higher in CWH than uninfected children in high-income and middle-income countries (7% in the USA,^10^ 32% in Brazil^11^ and 24% in Thailand^12^) compared with 1% in children without HIV in the USA.^10^ No study has estimated the prevalence of low BMD in SSA, and the prevalence of and risk factors for low BMD in African CWH are not known.^6 13^ It is important to highlight that the risk of poor bone accrual, reflected in low BMD measurements, is likely to be different in low-income countries compared with high-income countries due to factors such as malnutrition and social deprivation, but critically due to delayed ART initiation. A recent meta-analysis has shown that the median age of ART initiation in North America is 1 year, compared with 8 years in SSA.^14^

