Another mechanism by which HIV may exert effects on BMD is through its effect on puberty. Even in the presence of ART, the onset of puberty is delayed by approximately a year in CWH in both high-income^30^ and low-income settings.^31^ Older age at ART initiation has been shown to be a significant risk factor for pubertal delay in Zimbabwean CWH.^31^ Pubertal delay in HIV may be mediated through nutritional deficiency, recurrent infection or chronic immune activation disrupting hormonal regulation.^31^ Delayed puberty may be advantageous for linear growth; spending more time in puberty may allow more time for skeletal growth.^31^ Conversely, delayed puberty has been shown in studies in high-income settings to be detrimental to bone mass accrual.^32 33^ However, the impact of pubertal delay on BMD in low-income countries remains unknown. Pubertal delay can be assessed objectively using hand radiographs. Analysis of the growth plate development and fusion of long bones in the hands can accurately quantify bone age, which is a measure of skeletal maturation. Bone age lagging behind chronological age reflects pubertal delay.^34^

BMD is commonly measured by dual-energy X-ray absorptiometry (DXA) as two-dimensional (areal) BMD; however, this is highly dependent on bone size.^35^ DXA underestimates areal bone density in short children, with smaller bones, and overestimates BMD in taller children, with bigger bones, despite the fact that they may have identical volumetric BMD. Size adjustment of DXA measures is therefore critically important in children with chronic diseases such as HIV, where smaller size due to poorer growth and delayed puberty may explain findings of lower BMD. The two ‘gold standard’ size-adjustment techniques chosen from the International Society for Clinical Densitometry are as follows: bone mineral apparent density at the lumbar spine (LS BMAD) and regression based total-body less-head (TBLH) bone mineral content (BMC) for lean mass adjusted for height (TBLH BMC^LBM^)^36^ Z-scores. As there are currently no published reference DXA data for child or adolescent populations in SSA, in this study we will use the best available data sets from high-income countries such as the UK^36^ to generate Z-scores.

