	Bone architecture	Peripheral quantitative computed tomography (pQCT)	Trabecular and cortical vBMD (g/cm^3^), total and cortical CSA (mm²), cortical thickness (mm), periosteal and endosteal circumference (mm), SSI (mm^3^), PMI (mm^4^) and CSMI (mm^4^)
Blood tests	Bone markers and DNA	Blood test (DNA extraction and serum saved)	Future testing e.g. Vitamin D, alkaline phosphotase, C-terminal telopeptide (CTX)‡‡
	HIV markers	Blood test	CD4 count, HIV viral load†

*Details of treatment and comorbidities will be confirmed by patient-held medical records where available.

†Denotes assessments to be carried out in HIV-infected participants only.

‡Energy requirements defined in METS (multiples of the resting metabolic rate that give a score in MET-minutes).

§Nutritional indicator to include composite information from history (usual diet last month, sun exposure–vitamin D status) and clinical examination (MUAC). Similar methods have been used in other low-income contexts.^46^

¶Age-specific and sex-specific Z-scores for (1) anthropometric measures will be determined using the WHO child growth standards.^59^ (2) Hand grip strength will be determined with reference to the uninfected comparison group and European normative data.^60^ (3) Jumping distance will be determined using normative data from South Africa.^61^ (4) Low BMD will be determined with reference to published paediatric Hologic DXA reference databases for LS BMAD and TBLH BMC^LBM^ Z-scores.^36^

**Standing long jump; the longest distance after two attempts will be recorded.

††Pregnancy urine dipstick in female participants prior to DXA if uncertain pregnancy status.

‡‡Tests to be carried out on stored blood when further funding is secured.

CSA, cross-sectional area; CSMI, cross-sectional moment of inertia; DXA, dual-energy X-ray absorptiometry; LS BMAD, lumbar spine bone mineral apparent density; PMI, polar moment of inertia; SSI, Strength Strain Index; TBLH BMC^LBM^, total-body less-head bone mineral content for lean mass adjusted for height.

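### Low grip strength and low long jump are judged for age and sex with no body-size term, so a difference by HIV status may partly reflect shorter stature; a size-adjusted companion estimate is needed

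*Protocol article*

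**What the plan says.** All places are in the protocol article.

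- **Outcome measures (secondary):** "Prevalence of low muscle function; grip strength and standing long jump-for-age", with low meaning a Z-score below −2, by HIV status at baseline.
- **Table 1 footnote on Z-scores:** it opens with "Age-specific and sex-specific Z-scores for (1) anthropometric measures will be determined using the WHO child growth standards" and continues, under the same age- and sex-specific heading, with "Hand grip strength will be determined with reference to the uninfected comparison group and European normative data" and "Jumping distance will be determined using normative data from South Africa". Neither reference is said to condition on height or lean mass.
- **Study design:** the comparison group is frequency-matched on age and sex. Height plays no part.
- **Introduction:** "Poor linear growth (ie, stunting) is one of the most common manifestations" of perinatal HIV, affecting up to half of children. On densitometry it says: "Size adjustment of DXA measures is therefore critically important in children with chronic diseases such as HIV, where smaller size due to poorer growth".
- **Table 1 (pQCT row):** besides trabecular and cortical volumetric density, the list has total and cortical cross-sectional area, "cortical thickness (mm), periosteal and endosteal circumference (mm"), strength strain index, and polar and cross-sectional moments of inertia.
- **Statistical analysis:** pQCT, grip and jump data in children with HIV are to be read against the uninfected comparator. The only adjustment covariates listed for comparing the groups are physical activity, calcium and vitamin D intake, and they follow the DXA change models.
- **Discussion:** poverty and early nutrition, whatever the HIV status, may account for some of the shortfall in final height.

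**The concern.** Taller children of a given age and sex tend to grip harder and jump further. If children with HIV are shorter on average, a cut-off that conditions only on age and sex will classify more of them as having low muscle function, even if their strength is normal for their size. The outcome as defined mixes these two explanations, and matching on age and sex does nothing to separate them.

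The same applies to the baseline comparison of tibial geometry and strength indices. The Introduction's case for pQCT is that it handles bone size by measuring volumetric density. That covers volumetric density, but not areas, circumferences or moments of inertia, which grow with the bone.

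At stake is the interpretation of part of the Study hypothesis, which speaks of reduced strength and muscle function as well as bone mass. A deficit could be reported as impaired muscle or bone strength when some of it is short stature. By the article's own account, part of that short stature may not come from HIV.

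**Working it through.** The plan gives no figure of its own to reproduce here. The Sample size section deals only with DXA outcomes, and no height gap or height–strength slope is stated anywhere. What follows is an illustration with assumed inputs.

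**Grip and jump**

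Inputs:
- Cut-off −2 (Outcome measures); 300 children per group (Study design).
- Assumed: muscle Z-scores are normal with mean 0 and SD 1 in children without HIV.
- Assumed: children with HIV are shorter by D height-Z units, with D = 0.5 to 1.0.
- Assumed: slope of muscle Z on height Z is r = 0.4 to 0.6.
- Assumed: no HIV effect at a given height, and SD still 1.

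Formula: prevalence below −2 in children with HIV = Φ(−2 + D × r).

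| D | r | shift D × r | Φ(−2 + shift) |
|---|---|---|---|
| 0 | – | 0 | 2.3% |
| 0.5 | 0.4 | 0.20 | Φ(−1.8) = 3.6% |
| 1.0 | 0.5 | 0.50 | Φ(−1.5) = 6.7% |
| 1.0 | 0.6 | 0.60 | Φ(−1.4) = 8.1% |

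With 300 per group and a two-sided 5% comparison of proportions, 2.3% against 6.7% comes out significant about 74% of the time, with no deficit in strength for size. At a weaker setting (D = 0.5, r = 0.3, shift 0.15) the prevalence is 3.2% and the chance is about 10%. At a more extreme one (D = 1.5, r = 0.7, shift 1.05) it is 17.1% and close to certain. Under the same model, the expected HIV difference after adjustment for height is zero.

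**Tibial geometry**

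Assume purely proportional scaling, with a tibia 5% smaller in every dimension and identical material and shape:
- area (mm²): 0.95² = 0.90, about 10% lower;
- strength strain index (mm³): 0.95³ = 0.86, about 14% lower;
- moments of inertia (mm⁴): 0.95⁴ = 0.81, about 19% lower.

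Volumetric density is not affected in this way. The 1-year outcomes for cross-sectional area, cortical thickness and bone strength are percentage changes, which remove much of the baseline size difference. The point therefore bears mainly on the cross-sectional comparison named in Study objectives.

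**The case against.** The strongest counter-argument concerns the estimand. The article treats stunting as a manifestation of perinatal HIV, and the hypothesis is that children with HIV have reduced strength and muscle function. That is a total effect, and a for-age comparison with age- and sex-matched children addresses it. Height may lie on the causal path, so conditioning on it asks a different question. This stands: the for-age result should stay, and the adjusted estimate should not replace it. It does not remove the need for the companion estimate, because the Discussion itself names causes of short stature that are independent of HIV.

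Several stronger readings are tempting, but the documents do not support them.

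- *The article breaks its own size-adjustment rule.* That sentence concerns DXA, where areal density misstates true density because it is a two-dimensional measure. A weak grip is a real functional finding whatever its cause, and the Introduction links weak grip as such to falls and fractures in adults. Extending the reasoning to muscle is a fair inference, but there is no contradiction in the text.
- *Tibial geometry will be compared unadjusted.* No pQCT model is given at all, and covariates may be set in the full protocol or analysis plan. It can only be said that no size covariate is named here.
- *The study cannot tell short stature from weakness.* The stated outcome cannot, but the data can: height, lean mass and tibial length are all measured.
- *The Discussion's physiotherapy remark rests on this comparison.* It concerns muscle function as a predictor of size-adjusted bone density, and it calls for formal investigation.

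The planned look at pubertal delay helps only in part: it concerns changes in the bone and muscle outcomes, not baseline prevalence or body size.

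**Conclusion.** The point holds for grip strength and standing long jump. The outcome is fixed as an age- and sex-specific cut-off with no body-size term, in groups not matched on height, where stunting is common in one of them. A difference by HIV status may partly reflect stature. It need not do so, and the documents do not show by how much. Under the stated assumptions the contribution is a prevalence of about 3.6–8.1% against 2.3%. Outside that range of inputs it runs from minor to decisive. The 2.3% baseline also assumes that the reference fits the uninfected children, which is uncertain for European or South African norms.

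For baseline tibial geometry and strength indices the point is weaker, since it rests on a covariate not being named rather than on an analysis that is stated. These are secondary outcomes and objectives. The primary DXA outcomes are already size-adjusted and are not touched.

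**What to change.** 1. Keep the prevalence of for-age Z below −2, and describe it as the total difference by HIV status.
2. Beside it, report the HIV difference in grip strength and in jump distance from regression on age, sex and height.
3. For the baseline comparison of cross-sectional areas, cortical thickness, circumferences, strength strain index and moments of inertia, add an estimate adjusted for age, sex and tibial length. Leave volumetric density as it is. The percentage-change outcomes have less need of this.
4. State how to read the pair: the adjusted estimate is the difference between children of a given size. Muscle or bone-strength impairment beyond short stature is claimed only where the size-adjusted result supports it.

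The cost is a few sentences of analysis wording and some extra table columns. Height is measured under Clinical examination, and tibial length under Radiological assessments to place the scan sites, so no new data are needed. The downside is that height may mediate the effect of HIV, so neither estimate can be shown alone.

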### Sample size

The sample size was calculated to detect differences in DXA-measured mean size-adjusted bone BMD Z-scores between children with and without HIV. This study will have 80% power (α 0.05) to detect a 0.23 Z-score difference between 300 HIV-infected and 300 uninfected children, assuming an SD of 1.3. As there were no published studies from low income countries, estimates of the expected difference were taken from a US study of children with HIV aged 7–15 years.^10^ In addition, our study will have 80% power to detect a 4.8% difference in the prevalence low size-adjusted BMD between the two groups. This is a smaller prevalence difference than that detected by the most conservative prevalence estimate of low BMD of 7% from three studies in high-income and middle-income countries.^10–12^

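### The 4.8-point detectable difference in low-BMD prevalence rests on an unstated uninfected prevalence of about 2.2–2.3%, which does not agree with the SD of 1.3 in the same paragraph unless uninfected children average about +0.6 Z

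*Protocol article*

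**What the plan says.** The Outcome measures section lists two primary outcomes: mean size-adjusted Z-scores, and the baseline prevalence of Z-scores below −2.

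The Sample size section covers both. For the mean it claims 80% power at alpha 0.05 for "a 0.23 Z-score difference between 300 HIV-infected and 300 uninfected children", "assuming an SD of 1.3". For prevalence it adds that "our study will have 80% power to detect a 4.8% difference in the prevalence low size-adjusted BMD between the two groups". It supports the second figure with this sentence: "This is a smaller prevalence difference than that detected by the most conservative prevalence estimate of low BMD of 7" per cent, taken from studies in high-income and middle-income countries.

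The section gives no prevalence for uninfected children and no mean Z-score. The one uninfected prevalence in the article is in the Introduction, where 7% in US children with HIV is set beside other countries' figures, "compared with 1% in children without HIV in the USA". The Introduction also says that Z-scores will come from high-income reference data such as the UK's, because no reference data exist for children in sub-Saharan Africa.

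**The concern.** The detectable difference between two proportions depends on the comparator proportion as well as on sample size, alpha and power. A figure of 4.8 points therefore carries a hidden assumption about how many uninfected children fall below −2. Because low BMD is a tail of the Z-score distribution, that assumption should agree with the distribution used for the mean a sentence earlier. On the face of it, it does not.

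At stake is how a primary outcome will be read. If the true uninfected prevalence is well above 2.3%, the study has less than 80% power at 4.8 points, and a null prevalence result could be taken to exclude a difference that it cannot exclude.

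**Working it through.** **Inputs.** From the Sample size section: n = 300 per group, alpha 0.05, power 80%, SD 1.3, detectable differences of 0.23 Z and 4.8 points. From the Introduction: 1% (uninfected) and 7% (with HIV), both US. My assumptions: two-sided test, normally distributed Z-scores, no continuity correction. z₀.₉₇₅ = 1.960 and z₀.₈₀ = 0.842.

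**1. Reproduce 4.8 points.** With uninfected prevalence p₀, p₁ = p₀ + δ and p̄ = (p₀ + p₁)/2:

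n = [1.960·√(2p̄(1−p̄)) + 0.842·√(p₀(1−p₀) + p₁(1−p₁))]² / δ²

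- Take p₀ = 0.0228 and δ = 0.048, so p̄ = 0.0468. The roots are 0.2987 and 0.2968, and n = (1.960 × 0.2987 + 0.842 × 0.2968)² / 0.048² = 303 per group. With 300, power is 79.6% and the detectable difference is 4.83 points.
- Solving for exactly 4.8 points gives p₀ = 2.24%. With unpooled variance it is 2.28%, with the arcsine method 2.5%, and with a continuity correction 1.6%. A one-sided test would give 3.6%.
- For comparison, Φ(−2) = 2.28%: the share of a normal distribution with mean 0 and SD 1.0 below −2.

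So 4.8 points is reproducible, and it implies an uninfected prevalence of about 2.2–2.3%.

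**2. Compare with the Introduction's 1%.** At p₀ = 1% the detectable difference is 3.9 points, and power at 4.8 points is 90%. The contrast of 7% with 1% is 6 points and has 96% power.

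**3. Compare with the SD of 1.3.** The uninfected prevalence is p₀ = Φ((−2 − mean)/1.3). With 300 per group:

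| Mean Z, uninfected | p₀ | Detectable difference | Power at 4.8 points |
|---|---|---|---|
| +0.6 | 2.3% | 4.8 points | 80% |
| +0.3 | 3.8% | 5.7 points | 68% |
| 0 | 6.2% | 6.7 points | 55% |
| −0.5 | 12.4% | 8.5 points | 38% |

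With mean 0, Φ(−2/1.3) = Φ(−1.538) = 6.2%, and about 534 per group would be needed for 80% power at 4.8 points.

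**4. Check the SD in its own sentence.** Detectable mean difference = (1.960 + 0.842) × SD × √(2/300).

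- SD 1.3: 2.802 × 1.3 × 0.0816 = 0.297. Power at 0.23 is Φ(0.23/0.1061 − 1.960) = 58%, and 502 per group would be needed.
- SD 1.0: 2.802 × 0.0816 = 0.229. Power at 0.23 is 80.4%, and 297 per group are needed.
- A one-sided test with SD 1.3 gives 0.264, so sidedness does not explain the gap.

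Both printed detectable differences, 0.23 Z and 4.8 points, therefore follow from SD 1.0 (the second with mean 0). Neither follows from SD 1.3 with mean 0.

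**The case against.** A reader might infer that the SD of 1.3 rules out the 4.8-point figure, so that the true value is 6.7 points with 55% power. The article does not support that. A tail probability needs a mean and a distribution as well as an SD, and the article fixes neither. It attaches 1.3 to the mean comparison only, and does not say that it describes the uninfected group or that 4.8 was derived from it. SD 1.3 with a mean of +0.6 gives 2.3%. That objection stands, although nothing in the article suggests such a mean. The Introduction, which cites malnutrition and social deprivation, points the other way.

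Second, the only uninfected prevalence in the article is 1%, at which 4.8 points would be conservative. That also stands, so the direction of the error is not settled. But 1% is a third value, which agrees with neither 2.3% nor SD 1.3.

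Third, the 7% sentence might look like a plain error, because it sets a difference beside a single prevalence. Read with the Introduction's 7% versus 1%, it compares 4.8 with 6 points and is true. It is awkward, not false.

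Fourth, the sample size was set on the mean, and a condensed article may leave detail to the full protocol. That would excuse the missing comparator prevalence by itself. It does not excuse figures printed in one paragraph that do not agree with each other.

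**Conclusion.** The point holds as an inconsistency. The 4.8-point claim needs an uninfected prevalence of about 2.2–2.3% (two-sided, no continuity correction). That value is not stated, differs from the 1% in the Introduction, and agrees with the printed SD only if uninfected children average about +0.6 Z.

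The size of the error is conditional. If SD 1.3 describes the uninfected group and Z is normal, power at 4.8 points falls below 80% for any mean below about +0.6, as tabulated above. If the SD is really 1.0 with mean 0, 4.8 points is right. Since 0.23 Z also needs an SD of about 1.0, the printed 1.3 is more likely at fault than either detectable difference. Simply replacing 4.8 by 6.7 would change a figure that agrees with 0.23 Z and keep the input that does not.

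**What to change.** Reword the Sample size section so that one stated mean, SD and uninfected prevalence support both figures. Either:

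- use SD 1.0, mean 0 and an uninfected prevalence of 2.3%, in which case 0.23 Z and 4.8 points both stand; or
- keep SD 1.3 and restate both: 0.30 Z, and about 6.7 percentage points (6.2% versus 12.9%) if the mean is 0, with that mean declared.

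In either case, say where the SD comes from and which group it describes. Because the uninfected prevalence on a high-income reference is unknown, show the detectable difference over a range of 1–12%: about 3.9 points at 1%, 4.8 at 2.3%, 6.7 at 6.2% and 8.5 at 12.4%. Word the supporting comparison as 7% versus 1%, a 6-point contrast.

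The cost is rewording only. Under the second option the stated figures are less favourable. Neither option requires more children or a change to the analysis.
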